## Abstract

**Background:**

India is undergoing a significant demographic shift, with the elderly population (60+) projected to reach 20% by 2050. Tribal populations, such as those in Jharkhand, face accumulated disparities, including premature aging, lower life expectancy (63.9 years), and a dual burden of communicable and non-communicable diseases. Despite these challenges, there is a substantial research gap regarding early-onset functional decline—often beginning at age 45 due to physical labour and undernutrition—and the lack of culturally adapted healthcare models for these underserved groups.

**Objectives:**

This study aims – Phase 1 (Needs Assessment): Assess functional decline, quality of life (QoL), and prevalent health conditions/risk factors among middle-aged and elderly tribal adults in East Singhbhum, Jharkhand and Phase 2 (Model Development): Design and evaluate the feasibility and acceptability of a culturally sensitive, community-based integrated healthcare model to improve functional ability and QoL.

**Methods:**

The study employs a two-phase concurrent mixed-methods study design. Setting & Participants: Conducted in 25 villages across five tribal-dominated 5 blocks of East Singhbhum, targeting 520 tribal individuals aged 45 years and above. In Phase 1, Quantitative Component: A cross-sectional needs assessment will use tools like Barthel’s Activity of Daily Living (ADL), Lawton’s Instrumental Activities of Daily Living (IADL), and WHOQOL-BREF to establish baseline health and functional data. Qualitative Component: In-depth interviews, focus group discussions, and key informant interviews with community members, traditional healers, and health workers will explore contextual barriers and cultural perceptions of aging. Quantitative and qualitative findings will be analysed independently and integrated to identify priority domains for healthcare model development. In Phase 2, these findings will inform the co-development of a culturally sensitive, community-based integrated healthcare model through stakeholder consultation. The model will subsequently be implemented in a selected village to assess its effectiveness, feasibility, and community acceptability before refinement.

**Expected Outcomes:**

The study will establish critical baseline data on tribal aging and develop a validated, scalable healthcare model. Expected results include improved health service utilization, early detection of functional decline, and policy-level impact on geriatric and tribal health strategies in India.

**Conclusion:**

By prioritizing vulnerable populations and integrating indigenous knowledge with formal health systems, this protocol aligns with Sustainable Development Goals (SDGs 3, 10, and 17) to promote social equity and lifelong well-being for India’s tribal communities.

## Introduction

India is undergoing a major demographic and epidemiological transformation, with an increasing proportion of its people reaching middle and old age. The population aged 60 and above is predicted to increase considerably, rising from 8.6% in 2011 to nearly 20% by 2050, indicating a significant demographic shift towards an older population [1]. This trend is accompanied by an increase in chronic noncommunicable diseases, functional limits, and social vulnerabilities, which disproportionately affect underprivileged people, such as Scheduled Tribes. The ageing trajectory and health burdens of tribal groups, particularly in resource-constrained and physically isolated locations such as Jharkhand, have yet to be thoroughly investigated via empirical research [2].

Geographic, socio-cultural, and economic constraints frequently result in accumulated disparities within tribal communities. These variables can contribute to premature ageing, undiagnosed chronic diseases, and low quality of life, necessitating early detection and care [3]. Functional decline, defined as a decreased capacity to execute basic and Instrumental activities of daily living IADLs), is a strong predictor of disability, healthcare demands, and reduced independence in later life [4]. Quality of life, which is determined by physical, emotional, social, and environmental aspects, is also important in comprehending the whole experience of ageing [5].

The tribal population in India has much lower wellness scores than the mainstream population, the projected life expectancy from birth is 63.9 years versus 67 years countrywide [6]. Communicable diseases disproportionately afflict tribal people, accounting for 80% of malaria cases and 50% of associated deaths. The disease burden of pulmonary tuberculosis in tribal groups is substantially higher, at 703 per 100,000, compared to 256 per 100,000 in the general population. Noncommunicable diseases such as hypertension, diabetes, cardiovascular disease, and cancer are increasingly being reported in tribal areas. Particularly Vulnerable Tribal Groups (PVTGs) have high rates of malnutrition and genetic diseases such as sickle cell anaemia and G6PD deficiency [7].

In India, older adults are predominantly located in rural areas., which have a significantly greater prevalence of functional disability (34.3%) than urban areas (29.9%). Despite this gap, research has primarily concentrated on nutritional status and morbidity, with little emphasis on functional status. There is still a major vacuum in studies that especially address functional disability among the rural elderly [4].

Considering these developments, the current study seeks to assess functional decline, identify prevalent health disorders and risk factors, and evaluate quality of life among middle-aged and elderly tribal adults in selected districts of Jharkhand. The findings will provide the basis for developing culturally relevant, community-based care models in tribal settings that promote healthy ageing and prevent long-term dependency.

## Literature review

Tribal groups in India have unique health and social challenges, particularly as they age. A growing body of literature has identified these disparities and gaps in health service delivery, which this study aims to address through a community-based integrated care approach tailored to indigenous people.

To achieve universal health coverage, Reddy K.S. suggested significant changes to India’s healthcare system. They emphasized prioritizing vulnerable groups and investing in grassroots health systems, which is consistent with the study’s goals of delivering equitable care to senior tribal members.

Soren studied the impact of social isolation, comorbidities, and economic dependency on the Quality of life of old people in a tribally dominant state. This emphasizes the importance of multidimensional care, as promoted by this paradigm [3].

Kumar assessed frailty among old tribals, revealing early functional decline caused by poor diet and rigorous labor. The findings bring attention to the necessity of implementing preventive approaches and regular health assessments in vulnerable communities, which this approach aims to overcome [1].

Roy evaluated the issues faced by India’s tribal health system and compared them to global healthcare norms. Their research focuses on systemic concerns such as inadequate healthcare infrastructure, cultural hurdles, and poor healthcare access greatly affects tribal groups.. The authors underline the significance of culturally relevant healthcare interventions, as well as major investments in tribal health infrastructure, to close these gaps. Their findings are consistent with the goals of this study, which aims to address these disparities for older Indigenous populations using a culturally relevant, community-based integrated care strategy [2].

Negi highlighted the double burden faced by tribal communities in India due to historical marginalization and inadequate access to healthcare services. Despite their rich heritage of traditional healing practices, tribes are increasingly experiencing a loss of cultural health knowledge alongside limited outreach of modern medical systems. The authors emphasize that tribal populations are disproportionately affected by both communicable and non-communicable diseases, compounded by poor infrastructure, low literacy, and socio-economic deprivation. The study argues for the integration of traditional health systems with modern public health approaches to ensure culturally appropriate and effective care. It concludes with a call for context-sensitive policies and inclusive health strategies tailored to the unique needs of India’s tribal populations [3].

The Longitudinal Ageing Study in India (LASI), launched in 2017–18 by the Ministry of Health and Family Welfare in collaboration with IIPS, Harvard University, and USC, stands as the first nationally representative survey to comprehensively assess health, functional status, and quality of life among individuals aged 45 and above. While LASI provides critical insights into the ageing process in India, there remains a significant data gap concerning the early onset of functional decline and associated determinants among middle-aged and elderly tribal populations, especially the Particularly Vulnerable Tribal Groups (PVTGs) [5].

## Research gap identified

Inadequate Customization of Health Policies for Tribals (Reddy et al., 2020): Research in this area is currently sparse on how universal health policies (like UHC) can be adapted to suit the distinct sociocultural and infrastructural realities of tribal populations, particularly the elderly.

Neglect of Psychosocial Determinants of Ageing (Soren et al., 2022): Elderly tribals’ quality of life is insufficiently studied, especially factors like social isolation, economic dependence, and erosion of traditional community support systems.

Limited Understanding of Functional Decline and Frailty (Kumar et al., 2023): Research on frailty, nutritional status, and the impact of lifelong physical labor on functional capacity in tribal elders is sparse, leading to poor early identification and intervention.

Weak Integration of Traditional and Modern Healthcare Systems (Deb Roy et al., 2023): There’s a clear gap in how indigenous tribal health practices can be scientifically studied and effectively integrated with formal health systems without compromising cultural identity.

Lack of Context-Specific, Empirical Tribal Health Research (Emerald, 2021): Existing studies do not adequately capture the structural barriers, cultural nuances, and geographical challenges that shape health-seeking behavior and outcomes in tribal regions. Empirical, on-ground evidence is missing.

## Objectives

### Primary objective

#### Phase 1-Needs assessment.

To assess functional decline and determine prevalent health conditions and risk factors among middle-aged and elderly tribals, in selected blocks of East Singhbhum district.To evaluate the quality of life and associated health determinants, including prevalent risk factors, among the same population groups in the study area.

### Secondary objective

#### Phase 2- Healthcare model development.

3. To design a community-based, culturally sensitive healthcare model to assess its feasibility and acceptability in improving functional ability and Quality of life across middle-aged and elderly tribal populations across all the blocks of East Singhbhum.

## Detailed methodology

### Overall research design

The study will employ a two-phase mixed-methods implementation research design. Phase 1 will adopt a concurrent mixed-methods approach, in which quantitative and qualitative data will be collected simultaneously to comprehensively assess functional decline, quality of life, health conditions, healthcare utilisation, and socio-cultural determinants among middle-aged and elderly tribal populations in Jharkhand. The quantitative and qualitative findings will be analysed independently and integrated during interpretation to provide a comprehensive understanding of the community’s health needs. The integrated findings from Phase 1 will be used to identify, prioritise, and confirm the key domains that will underpin the development of the healthcare model in Phase 2 Fig 1. Building on these empirically derived domains, Phase 2 will focus on the co-development of a culturally sensitive, community-based integrated healthcare model through evidence synthesis and stakeholder consultation. This iterative process ensures that the proposed model is evidence-based, context-specific, and responsive to the health priorities, cultural practices, and service needs of tribal [8].

**Fig 1 pone.0358356.g001:**
[figure not shown]
Overview of the concurrent mixed-methods study design integrating quantitative and qualitative components for assessing functional decline and quality of life, informing the development of a community-based integrated healthcare model.

### Trial registration

The study has been prospectively registered with the Clinical Trials Registry–India (CTRI) (Registration No. CTRI/2026/04/108631).

### Study setting

The study will be conducted in East Singhbhum district, Jharkhand, India, a tribal-dominated district with substantial populations of Scheduled Tribes (STs) and Particularly Vulnerable Tribal Groups (PVTGs). Data collection will be undertaken across five tribal-dominated blocks—Golmuri–Jugsalai, Potka, Ghatshila, Dhalbhumgarh, and Ghurabandha—to capture the district’s geographical, socio-cultural, and healthcare diversity. Using a multistage sampling approach, 25 villages (five villages per block) will be selected to ensure comprehensive within-district representation and to generate evidence for the development of a culturally sensitive, community-based integrated healthcare model for middle-aged and elderly tribal populations.

### Study population

The study population will comprise tribal individuals aged 45 years and above residing in rural and tribal-dominated regions of East Singhbhum district, Jharkhand, including both men and women belonging to Scheduled Tribes (STs) and Particularly Vulnerable Tribal Groups (PVTGs). Individuals aged 45 years and above have been selected because tribal populations in India experience premature ageing due to chronic undernutrition, physically demanding occupations, poverty, environmental hardships, and limited access to healthcare services. Consequently, functional decline, multimorbidity, and other age-related conditions often occur earlier than in the general population. Restricting the study to individuals aged 60 years and above may therefore overlook a substantial proportion of tribal adults already experiencing early functional impairment and poor quality of life. Furthermore, the relatively lower life expectancy among tribal populations (approximately 62–65 years) supports the inclusion of middle-aged adults to enable earlier identification of health needs and generate evidence for the development of a culturally sensitive, community-based integrated healthcare model.

### Eligibility criteria

Inclusion

The participant must be 45 years of age or older.The individual should belong to a Scheduled Tribe (ST) or a Particularly Vulnerable Tribal Group (PVTG).The participant must have been a continuous resident of the selected area for at least five years.The participant must participate voluntarily in the study and able to provide informed consent

Exclusion

Individuals who have severe cognitive impairment that prevents them from understanding or responding to interview questions will be excluded from the study.Participants who are currently enrolled in similar health-related interventions or research studies will not be included, to avoid duplication and potential bias in the findings.

### Sample size

#### Quantitative component.

The sample size was determined using Cochran’s formula for large populations, utilizing the reported 34.3% prevalence of functional disability among rural older adults from the Longitudinal Ageing Study in India (LASI) Wave 1 as the reference estimate [5].

This reference proportion (p) was applied alongside a 95% confidence level and a 5% margin of error to calculate an initial requirement of 346 participants. To account for the multistage cluster sampling design, a design effect of 1.5 was applied, resulting in a final target sample size of 520. The formula used here is as follows:

$$\begin{array}{c} n\;=\frac{\left(z^{\text{2}}*\;\hat{p}\left(\text{1}\;-\;\hat{p}\right)\right)}{\varepsilon^{\text{2}}}\;(\text{4}) \end{array}$$

where:

n = required sample sizeZ = 1.96 (95% confidence level)p = 0.343 (estimated prevalence of functional disability)1 − p = 0.657d = 0.05 (absolute precision)

Substituting these values:

n=(0.05)2(1.96)2×0.343×0.657=346

As the study will employ a multistage cluster sampling approach, a design effect (DEFF) of 1.5 was applied to account for clustering of observations. This yielded a final sample size of:

346 × 1.5 = 519

which was rounded to **520 participants.**

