### Sampling strategy

#### Quantitative component.

A multistage stratified random sampling strategy will be employed for the quantitative component. In the first stage, five tribal-dominated blocks of East Singhbhum district (Golmuri–Jugsalai, Potka, Ghatshila, Dhalbhumgarh, and Ghurabandha) will be included. In the second stage, five villages will be randomly selected from each block, resulting in a total of 25 study villages. The distribution of the sample across the five blocks and 25 selected villages is illustrated in Fig 2. Finally, eligible participants aged ≥45 years will be selected using proportionate allocation and systematic random sampling within each selected village until the required sample size is achieved Table 2–5.

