### Data collection procedure

The data collection for the mixed-method study will begin by obtaining necessary approvals from the Institutional Ethics Committee (IEC), Institutional Scientific Committee (ISC), and administrative permissions from the State Tribal Welfare Department, District Health Authorities, and Panchayat-level leaders in the selected districts. Community sensitization meetings will be held in each selected village to inform local leaders, ASHA workers, and residents about the study’s purpose and procedures, thereby building trust and encouraging participation. A household listing will be conducted to identify eligible individuals aged 45 years and above, including both middle-aged (45–59 years) and elderly (60 + years) participants. Informed consent will be obtained, and for illiterate participants, thumb impressions will be taken in the presence of a witness to ensure ethical participation.

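### The last stage of the 'stratified' survey leaves age and sex uncontrolled, and two sections differ on whether individuals or households are selected

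*Protocol article*

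**What the plan says.** **Who is sampled.** Under Eligibility criteria, "The participant must be 45 years of age or older". The Data collection method section names two bands in the target population, 45–59 and 60 and above.

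**How they are sampled.** The Sampling strategy section calls the design multistage stratified. All five blocks are included and five villages are drawn at random in each. Then "eligible participants aged ≥45 years will be selected using proportionate allocation and systematic random sampling within each selected village". The caption of Fig 2 mentions only blocks and villages. The Data collection method section (Quantitative component) words the last stage differently: either random or systematic selection as circumstances permit, with a household listing followed by every nth household as the example.

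**What the frame contains.** Under Data collection procedure, "A household listing will be conducted to identify eligible individuals aged 45 years and above", and that sentence goes on to name both age bands.

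**How age and sex are used.** The Detailed data analysis section compares mean scores across age categories, gives gender against functional decline as an example of an association test, adjusts the regression models for age and gender, and stratifies by gender where appropriate. Age stratification at the selection stage is stated only for the focus groups.

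**Sample size.** The calculation proceeds by "utilizing the reported 34.3% prevalence of functional disability among rural older adults", citing LASI Wave 1. "This reference proportion (p) was applied alongside a 95% confidence level and a 5% margin of error", and a design effect of 1.5 brings the total to 520.

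**The concern.** There are two weaknesses at the last stage of selection.

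First, the stratification stops at geography. The reason given for enrolling from 45 is that functional decline starts early in this population, so the split at 60 matters to the study's purpose. The listing identifies people in both bands, yet nothing described uses it to fix the sampled mix of age and sex.

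Second, the two sections do not agree on the unit selected. Sampling eligible individuals from a list gives each person in a village the same chance. Sampling every nth household does not, unless a rule says what happens inside the household. If one person is taken per household, people who live with other eligible adults are under-represented, and household composition is likely to be related to age. The age mix could then differ from that of the village on average, not just by chance.

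At stake are the age-sex composition of the sample, a small amount of precision in the pooled prevalence, and whether a reader can tell how participants were chosen.

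**Working it through.** **1. The plan's own figure.** Inputs from the Sample size section: z = 1.96, p = 0.343, d = 0.05, design effect 1.5.

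- n = 1.96² × 0.343 × 0.657 / 0.05² = 346.3
- 346.3 × 1.5 = 519.4 (the plan: 346 × 1.5 = 519, rounded to 520)
- Half-width at 520: 1.96 × √(0.343 × 0.657 × 1.5 / 520) = 5.0 points

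The stated figures reproduce. They are also robust to the choice of p: p = 0.20 would need 369 people, and at the worst case, p = 0.50, 520 people give ±5.3 points.

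**2. How far chance alone moves the age mix.** The protocol gives no share aged 60 and over, so 40% is assumed.

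- Standard error of the share: √(0.4 × 0.6 × 1.5 / 520) = 2.6 points; 95% range about ±5.2 points
- Effect on pooled prevalence = 5.2 points × age gap: about ±0.5 (10-point gap), ±1.0 (20-point gap), ±1.5 (30-point gap)

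This variation is part of p(1 − p) and so is already inside the pooled margin.

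**3. What sorting by age band would gain.** Half-width = 1.96 × √(V × 1.5 / 520). V is p(1 − p) without sorting, and p(1 − p) less the between-band variance with it. Worked case (assumed): 20% at 45–59, 50% at 60 and over, 60/40 mix.

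- Pooled p = 0.6 × 0.20 + 0.4 × 0.50 = 0.32; p(1 − p) = 0.2176
- Between-band variance = 0.6 × 0.4 × 0.30² = 0.0216, or 9.9% of the total
- Without sorting: 1.96 × √(0.2176 × 1.5 / 520) = 4.9 points
- With sorting: 1.96 × √(0.1960 × 1.5 / 520) = 4.7 points

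| Assumed prevalence, ≥60 / 45–59 (40% aged ≥60) | Unsorted | Sorted by age |
|---|---|---|
| 34.3% / 24.3% | ±4.74 | ±4.71 |
| 34.3% / 14.3% | ±4.38 | ±4.26 |
| 50% / 20% | ±4.91 | ±4.66 |

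**4. Individuals against households.** Take every nth household and then one eligible person in it. Someone who is the only eligible resident is chosen with probability 1/n. Someone who shares the house with one other eligible person is chosen with probability 1/(2n), half as often. Taking everyone eligible restores equal chances, but the number of participants per village is then not fixed in advance and members of one household enter together. The protocol does not say which applies.

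**5. Precision for those aged 60 and over (p = 0.343).** The first version keeps the design effect at 1.5. The second rescales it to the smaller take per village, using the intraclass correlation implied by 520/25 = 20.8 people per village: 0.5 / 19.8 = 0.025.

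| Assumed share ≥60 | n | Design effect 1.5 | Rescaled design effect | Half-width, rescaled |
|---|---|---|---|---|
| 30% | 156 | ±9.1 | 1.13 | ±7.9 |
| 40% | 208 | ±7.9 | 1.19 | ±7.0 |
| 50% | 260 | ±7.1 | 1.24 | ±6.4 |

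**The case against.** The case for leaving the design alone is strong on several counts.

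- **The word 'stratified' is not wrong.** All five blocks are included and villages are drawn within each, so blocks act as strata. Not stratifying by age is a choice, not a contradiction. This stands.
- **Proportionate systematic selection already gives the right age mix on average.** This stands if individuals are selected. A reader might infer that the pooled prevalence is at the mercy of a chance age mix, but step 2 shows ordinary sampling error of 0.5 to 1.5 points, already counted. A 10-point drift at a 40% share would be 10 / 2.63 = 3.8 standard errors. The argument does not cover the every-nth-household option.
- **Age is handled in the analysis**, by comparing age categories and adjusting the models. This stands, but it does not settle how people are chosen.
- **An article condenses the full protocol**, so a missing within-household rule might be found there. That is fair for the rule alone. It does not explain why two sections of the same article describe different units of selection.

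Two further inferences are tempting and not supported. One is that 34.3% is a figure for those aged 60 and over, applied wrongly to a population from 45. The Introduction does place it in a paragraph calling for "studies that especially address functional disability among the rural elderly", but it gives no age cut-off. The Literature review describes LASI as assessing "functional status, and quality of life among individuals aged 45 and above", the same lower limit as this study. The age base is unstated; a mismatch is not shown. The other is that the estimate for those aged 60 and over misses a ±5-point target. The plan sets that margin for one pooled proportion only, so the wider margins in step 5 are the ordinary price of a subgroup.

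**Conclusion.** The point holds as a modest design improvement plus one inconsistency to resolve. No described stage controls age or sex, although the listing identifies both age bands and both variables are analysis groups. The two descriptions of the last stage also differ on whether individuals or households are drawn.

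The precision at stake is small: about 4.9 to 4.7 points for the pooled half-width under an assumed 30-point age gap and 60/40 mix, and almost nothing under a 10-point gap. The larger benefits are a sampled age-sex mix that stays close to each village's own and a single, reproducible selection rule. The possible distortion from household sampling cannot be sized, because the protocol gives neither household composition nor a within-household rule.

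The sample size of 520 and the pooled ±5 points stand. For those aged 60 and over, a reader should expect roughly ±6.4 to ±9.1 points if they form 30–50% of the sample (assumed), depending on how the design effect is scaled.

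**What to change.** Use the same wording for the last stage in the Sampling strategy and Data collection method sections: in each village, list all eligible individuals, sort the list by age band (45–59, 60 and over) and sex, and take every nth person from a random start. Remove the every-nth-household option. This is implicit proportionate stratification. It adds no weights beyond any that the village stage requires.

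The cost is a sort of the listing that is already planned, a few words in two sections, and a switch to a list of persons wherever teams had meant to work by household. No participants are added, and the sample-size section needs no recalculation.

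The timeline gives recruitment as 15 May to 30 June 2026. For any village already sampled, record which procedure was used. If one person was taken per household, also record the number of eligible people in that household, so that unequal selection chances can be allowed for in the analysis.
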